**Simple Effects**			
**3. Family level predictors within risk and sex groups** (n = 356 / 267 / 623; effective n = 548 / 411 / 958)	0.120	0.139	0.091
**4. Child level predictors within risk and groups** (n = 712 / 534 / 1246; effective n = 1017 / 763 / 1780)	0.088	0.102	0.067

Power for tests 1 and 2 in the table apply to direct effects (**Aim 1** paths in Fig 1); mediation effects (products of path coefficients; **Aim 2** paths in Fig 1), and moderating effects (differences in slopes/interactions; **Aim 3** paths in Fig 1); Tests 3 and 4 represent simple slopes for associations within levels of the moderators family risk status and service member sex, which represent the lowest powered tests.

Some cite 0.10 as a “small” effect size for a partial correlation, which is comparable to a standardized beta coefficient [46]. Recent findings about effects of recent deployment (duration, trauma) effects on military youth outcomes gave standardized beta effect estimates in the range of 0.18 to 0.32, on average [44]. These reported effects were controlling for baseline levels in child outcomes and therefore represent effects on residual change, giving confidence that the study is adequately powered. Importantly, power will be further increased through the use of latent variables, which increase measure reliability [47], correlated mediators and outcomes in multivariate analyses [48], and including control variables that explain variance in mediators/outcomes (particularly true in panel analyses). However, power may decrease due to the unequal weighting effect [49].

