The sampling frame was constructed using probability methods from DoD personnel records by the Defense Manpower Data Center (DMDC) using information about family members in the Defense Enrollment Eligibility Reporting System (DEERS) and deployments in the Contingency Tracking System (CTS) and PERSTEMPO file. The sample was drawn to ensure representation of service branches, components (active or reserve), and paygrades (officer/enlisted) using a systematic sampling method. To compensate for their low representation in the military [43], female military parents were oversampled to comprise 65% of the sample using explicit stratification [42]. The sample also was stratified according to military parents’ exposure to adverse experiences, compensating for higher nonresponse typical of high risk groups. Based on national data, approximately half the military parents are expected to have experienced at least one of 12 adverse experiences prior to deployment [9]. Based on screening, each family is assigned to gender and risk groups as they enter the study. Interviewers are blind to participant risk group.

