### Sample size determination with statistical power calculation

Data will be obtained from 712 families at baseline, with 2 children and up to 2 parents per family (given divorce rates, 1.66 parents per family are estimated). Stratification will be used to over-select female service members and high-risk families such that 456 families will have female military parents and 356 families will be high risk. Power is calculated for three types of analytic samples:

A baseline/cross-sectional analysis sample of 712 families and 1,424 children (2 per family), and 1,182 parents (1.66 per family);A panel analysis sample composed of families who participate at both waves of the study. Based on experience and other military studies [44], 75% retention is projected, resulting in 534 families, 1,068 children, and 887 parents at Wave 2;A repeated measures sample, comprising all observations from both waves. With a 75% family retention rate, the sample will include 1,246 (= 712 + 534) repeated family observations and 2,670 repeated child observations, and 2,216 repeated parent observations. The repeated measures sample will be the priority sample for testing study hypotheses.

Effective sample sizes are calculated for a two-level, mixed-effects model per Snijders [45] using an estimated within-family ICC = 0.30. Power is estimated for a standardized regression coefficient in a model with 5 covariates and alpha = 0.05. Effect sizes detectable at .80 power are listed in Table 1.

**Table 1 pone.0295007.t001:** Detectable effect sizes.

Direct, Moderation, and Mediation Effects (n = cross-sectional / panel / repeated)	Detectible Standardized Beta		
	Cross- sectional	Panel	Repeated Measures
**1. Family level predictors** (n = 712 / 534 / 1246; effective n = 1095 / 822 / 1917)	0.085	0.098	0.064
**2. Child level predictors** (n = 1424 / 1068 / 2492; effective n = 2034 / 1526 / 3560)	0.063	0.072	0.047

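### Table 1 assumes 356 families in each sex group, but the sampling plan leaves only 256 with a male military parent, so the stated power does not hold for fathers' deployments

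*Protocol article*

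**What the plan says.** The section on sample size and power starts from 712 families: "Data will be obtained from 712 families at baseline, with 2 children and up to 2 parents per family". It then fixes the strata: "456 families will have female military parents and 356 families will be high risk". The Sample section gives the female share differently: "female military parents were oversampled to comprise 65% of the sample using explicit stratification".

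Table 1 lists the standardized betas detectable at 80% power. Under its Simple Effects heading, row 3 (family-level predictors) is labelled as applying within risk and sex groups and uses "n = 356 / 267 / 623; effective n = 548 / 411 / 958", with betas 0.120 / 0.139 / 0.091. Row 4 (child-level predictors) uses 712 / 534 / 1246 children, which at two per family is the same 356 / 267 / 623 families, with betas 0.088 / 0.102 / 0.067. Row 4's label mentions risk but not sex. The paragraph below the table, however, assigns both rows to family risk status and to service member sex, and describes them as the tests with the least power.

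**The concern.** A group size of 356 is exactly half of 712. That is right for risk, where 356 families are high risk and 356 are not. It is right for neither sex group: 456 families with a female military parent leave 256 with a male one. The table therefore overstates the male-parent group by 100 families and gives it a precision that the sample cannot deliver.

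Parent sex is a named moderator in Aim 3, and the Innovation section presents the comparison of mothers' and fathers' deployments as something the design makes possible. Oversampling mothers is what shrinks the fathers' group, and the power table does not show that cost. Recruitment is unlikely to repair it, because the Sample section excludes families whose stratum is already full, so the male number is set by design.

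The two statements of the female share add a smaller ambiguity: 65% of 712 is about 463 families, whereas 456 is 64.0%.

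**Working it through.** **Inputs, all from the protocol article**
- 712 families with two children each; 456 with female military parents, so 712 − 456 = 256 with male military parents.
- Retention: "75% retention is projected, resulting in 534 families, 1,068 children, and 887 parents at Wave 2".
- Clustering: "using an estimated within-family ICC = 0.30".
- Test: "Power is estimated for a standardized regression coefficient in a model with 5 covariates and alpha = 0.05". Sidedness is not stated; two-sided reproduces the table.
- Target power: "Effect sizes detectable at .80 power are listed in Table 1".

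**Formulas**, for F families and ICC = 0.30
- Effective n, family-level predictor: 2F / (1 + 0.30).
- Effective n, child-level predictor: 2F / (1 − 0.30).
- Detectable beta: (1.960 + 0.842) / √(effective n) = 2.80 / √(effective n).
- Power at a given beta: Φ(beta × √(effective n) − 1.96).

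**Step 1: reproduce the printed rows (F = 356 / 267 / 623)**
- Family level: effective n 548 / 411 / 958, an exact match; betas 0.1197 / 0.1382 / 0.0905, printed as 0.120 / 0.139 / 0.091.
- Child level: effective n 1017 / 763 / 1780, an exact match; betas 0.0878 / 0.1014 / 0.0664, printed as 0.088 / 0.102 / 0.067.
- Rows 1 and 2 also reproduce to within about 0.001. A Fisher z version with five covariates changes these betas by less than 0.001.

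**Step 2: male-parent families**

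Cross-sectional F = 256; panel 0.75 × 256 = 192; repeated 256 + 192 = 448.

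| | Cross-sectional | Panel | Repeated |
|---|---|---|---|
| Family level, effective n | 512/1.3 = 394 | 384/1.3 = 295 | 896/1.3 = 689 |
| Family level, beta | 0.141 | 0.163 | 0.107 |
| Printed, row 3 | 0.120 | 0.139 | 0.091 |
| Power at printed beta | 66% | 67% | 67% |
| Child level, effective n | 512/0.7 = 731 | 384/0.7 = 549 | 896/0.7 = 1280 |
| Child level, beta | 0.104 | 0.120 | 0.078 |
| Printed, row 4 | 0.088 | 0.102 | 0.067 |
| Power at printed beta | 66% | 67% | 67% |

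Worked example: Φ(0.120 × √394 − 1.96) = Φ(0.42) = 0.66. The inflation is the same in every column: √(356/256) = 1.18.

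**Step 3: female-parent families (F = 456 / 342 / 798)**
- Family level 0.106 / 0.122 / 0.080; child level 0.078 / 0.090 / 0.059. All are smaller than printed.

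**Step 4: the 65% figure**
- 0.65 × 712 = 462.8, leaving about 249 male-parent families. Family level becomes 0.143 / 0.165 / 0.108; child level 0.105 / 0.121 / 0.079.

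**The case against.** The strongest reply is that the adequacy conclusion survives. The plan rests it on published effects of 0.18 to 0.32, and even the worst corrected value (0.163, or 0.165 with 249 families) is below 0.18. Male-group power at 0.18 for family-level predictors is about 95% cross-sectionally, 87% in the panel and over 99% with repeated measures. This stands, on the plan's own assumptions. However, the cited effects concern recent deployments, whereas this study is about long-term consequences, and the plan concedes an unquantified loss from unequal weighting. In the repeated-measures sample, which the plan gives priority, the family-level value also moves from 0.091 to 0.107, across the 0.10 that the plan mentions as a small effect. The other two printed values in row 3 already exceeded that mark.

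A second reply is that the formal mother-father comparison uses multi-group likelihood ratio tests, and the plan assigns power for slope differences to rows 1 and 2. That is correct. The present error concerns the slopes within father-deployed families and shows nothing about the power of the difference test.

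Third, the error runs one way only: the risk figures are right and the female figures are conservative. That is also correct.

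Fourth, 65% and 456 differ by only seven families. The gap may be rounding, or 65% may describe the sample drawn rather than the families enrolled. It is a minor point, and one clear number would settle it.

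**Conclusion.** The concern holds. Rows 3 and 4 are presented as covering service member sex, but their group size exists only for the risk split. For families with a male military parent, the detectable simple slopes are about 18% larger than printed in every column, and power at the printed betas is 66 to 67% rather than 80%. The statement that the tabulated rows are the weakest tests is therefore also untrue, because the male-parent slopes are weaker.

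The consequence is bounded: one stratum is affected, and the general claim of adequate power against effects of 0.18 or more is not overturned.

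The figures assume a two-sided 5% test, the plan's ICC of 0.30 and 75% retention applying equally in the male stratum, no loss from weighting, and the table's own way of counting the two waves in the repeated-measures column.

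**What to change.** Replace rows 3 and 4 with separate lines for each grouping:
- **Risk groups (356 each):** the printed values stand.
- **Female military parent (456 families):** 0.106 / 0.122 / 0.080 at family level and 0.078 / 0.090 / 0.059 at child level.
- **Male military parent (256 families):** 0.141 / 0.163 / 0.107 at family level and 0.104 / 0.120 / 0.078 at child level.

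Amend the paragraph below the table to name the male-parent slopes as those with the least power. State the female target as one number in the Sample and power sections, either 456 or 65% (463), or explain that the two describe different things. If 463 is chosen, use 249 male-parent families and recompute both sex lines.

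The cost is a few table rows and a sentence. The male-parent figures become less favourable and the female-parent figures more so. No families are added, and neither the design nor the analysis changes.

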#### Analyses for aim 2: To assess the role of parents’ psychological health and family processes in mediating relationships between siblings’ early exposures to parental deployment and later youth adjustment

This aim highlights four indirect pathways through which deployment(s) influence youth adjustment. Deployment factors studied in Aim 1 are expected to be negatively related to parents’ psychological health, parental efficacy, marital relationship quality, and family functioning at Time 1, which in turn will be positively related with youth adjustment at Time 2. The magnitude and statistical significance of the indirect effects of deployment through each of these processes will be tested using the INDIRECT command within Mplus, which employs a product of coefficients method of testing mediation [121] and the bootstrap method to compute standard errors for the significance test [122]. Importantly, the four indirect pathways will be tested concurrently, highlighting not only which pathways are critical for understanding the potential enduring effects of parental deployments on youth adjustment, but also the relationships among them. Differences across siblings also will be assessed.

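### Table 1's detectable effects are for one regression coefficient: they do not carry over to slope differences or indirect effects, and the simple slopes are not the weakest tests

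*Protocol article*

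**What the plan says.** The section on sample size determination describes one kind of calculation: "Power is estimated for a standardized regression coefficient in a model with 5 covariates and alpha = 0.05", with effective sample sizes from a two-level model "using an estimated within-family ICC = 0.30". It adds: "Effect sizes detectable at .80 power are listed in Table 1". The base sample is "A baseline/cross-sectional analysis sample of 712 families and 1,424 children (2 per family"), with 75% family retention at Wave 2.

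The text under Table 1 widens the scope. It says "Power for tests 1 and 2 in the table apply to direct effects", then adds mediation effects, defined as products of path coefficients, "and moderating effects (differences in slopes/interactions"). The table's own header names all three kinds of effect. Rows 3 and 4 are described as simple slopes within levels of "family risk status and service member sex, which represent the lowest powered tests".

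The analysis sections plan the following:
- **Aim 2:** mediators at Time 1 and outcomes at Time 2, a product-of-coefficients test, and "the bootstrap method to compute standard errors for the significance test".
- **Aim 3:** multi-group likelihood-ratio comparisons for parent and child sex, and conditional indirect effects for continuous moderators.

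**The concern.** A regression coefficient, a difference between two coefficients and a product of two coefficients have different standard errors. One detectable value cannot serve all three unless the scale is chosen so that it does, and the text names differences in slopes without stating any such scale. The lowest-powered sentence also conflicts with the table's own rows, because a contrast between two independent slopes is less precise than either slope alone.

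The model-building section uses alpha 0.05 to decide whether hypotheses are supported. Women were oversampled so that mothers' and fathers' deployments can be compared. A reader who trusts the stated figures could take a non-significant sex difference as evidence of no difference, when the test had much less than 80% power for a gap of the tabled size.

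**Working it through.** **Inputs (sample size section and Table 1).** Alpha 0.05 (two-sided assumed; this reproduces the table), power 0.80, ICC 0.30, 712 families with 1,424 children. Row 1 effective n is 1095 / 822 / 1917, row 2 is 2034 / 1526 / 3560, row 3 is 548 / 411 / 958. Female military parents in 456 families leave 712 − 456 = 256 with male military parents; 356 of 712 families are high risk.

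**1. The plan's own figures.** Effective n is child n/(1 + ICC) for family-level predictors (1424/1.3 = 1095) and child n/(1 − ICC) for child-level predictors (1424/0.7 = 2034). Detectable beta = (1.960 + 0.842)/√(effective n) = 2.80/√(effective n). Row 1 gives 0.0847 / 0.0977 / 0.0640 and row 3 gives 0.1197 / 0.1382 / 0.0905. All twelve cells agree within 0.002. The table is correct for a single coefficient.

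**2. Slope differences, categorical moderator.** The SE of the difference is √(1/n₁ + 1/n₂), with n₁ and n₂ the effective group sizes.
- 50:50, cross-sectional: √(1/548 + 1/548) = 0.0604; × 2.80 = 0.169. Table 1 alone gives the same answer: row 3's 0.120 × √2 = 0.170.
- Parent sex: n₁ = 456 × 2/1.3 = 702 and n₂ = 256 × 2/1.3 = 394; √(1/702 + 1/394) = 0.0630; × 2.80 = 0.176.

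| Slope difference at 80% power | Cross-sectional | Panel | Repeated |
|---|---|---|---|
| Family level, stated | 0.085 | 0.098 | 0.064 |
| Family level, 50:50 | 0.169 | 0.195 | 0.128 |
| Family level, 456/256 | 0.176 | 0.204 | 0.133 |
| Child level, stated | 0.063 | 0.072 | 0.047 |
| Child level, 50:50 (e.g. child sex) | 0.124 | 0.143 | 0.094 |

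Power for a difference of 0.085 is Φ(0.085/0.0604 − 1.96) = 29% at 50:50 and Φ(0.085/0.0630 − 1.96) = 27% at 456/256. Every slope difference exceeds the corresponding simple slope in row 3 or 4 (0.169 against 0.120; 0.124 against 0.088), so rows 3 and 4 are not the weakest tests.

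The plan cites direct effects of 0.18 to 0.32. A slope falling from 0.18 to 0.09 between equal family-level groups has 32% / 25% / 50% power. A fall from 0.18 to zero has 85% / 73% / 98%.

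**3. Scale.** For a moderator coded ±1 and split 50:50, the product term has the same SE as a main effect, so 0.085 is detectable as that coefficient. The slopes are then b₁ ± b₃, so the gap is 2 × 0.085 = 0.17, the same result as above. With two independent standardized continuous variables, the tabled beta holds for the product-term coefficient.

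**4. Indirect effects.** The two path z-statistics were simulated as independent normals (400,000 draws). The planned test was taken as ab/√(a²s_b² + b²s_a² + s_a²s_b²).
- Each path at its tabled beta (mean z 2.80): joint significance 0.80² = 64%; planned test 37%. A full bootstrap simulation at n = 822 gave 34.5% (600 replicates).
- For 80% power with the planned test, each path needs z of about 3.68, so 3.68/2.80 = 1.3 times the tabled beta: 0.111 / 0.128 / 0.084 at family level.
- Both paths 0.10, effective n 822: 67% joint, about 40% planned test.
- Both paths 0.18, first path on 534 families and second on effective n 822: 98.5% joint, 97% planned test.
- Tabled value read as the product itself, equal paths (√0.085 = 0.29 each): close to 100%.

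Where exposure and mediator both take one value per family, siblings add nothing to the first path. Its detectable beta is then 2.80/√712 = 0.105 on all families, or 2.80/√534 = 0.121 on the panel.

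**The case against.** A reader might infer that Aims 2 and 3 are both badly underpowered. The documents do not support that.

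- **Mediation.** The 64% and 37% figures require both paths to sit exactly at the tabled value. If the tabled value is the product of roughly equal paths, the table understates power; only very unequal paths reverse this (panel, product 0.098: 56% with a first path of 0.8, 28% with 0.9). At 0.18 for both paths, the low end of the cited range, the planned test is well powered. That range is for direct effects, so it does not establish the path sizes either.
- **First path.** A detectable first path of 0.105 is not general. Table 2 includes youth-reported mediators (parental acceptance, monitoring, family functioning, sibling relationship). Aim 1 includes child-specific exposures such as age at first deployment.
- **Continuous moderators.** Vulnerability and support are to be tested with continuous-moderator procedures, and a standardized product term keeps the main-effect SE. The slope-gap figures apply to categorical moderators. The analysis section names parent and child sex; risk status enters through the text under Table 1.
- **Multi-parameter tests.** The likelihood-ratio comparison may constrain several paths at once. The 27–29% describes a single slope difference.
- **Panel column.** It already exists, and the text does not expressly assign mediation to the repeated-measures column, although it calls that sample the priority.
- **Interpretation.** The plan says its focus will be on effect sizes and confidence intervals, which tempers the risk of misreading a null result.

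These points narrow the finding. They do not rescue the statement that rows 1 and 2 apply to differences in slopes, or the lowest-powered sentence.

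**Conclusion.** The finding stands in narrow form. The text under Table 1 attributes a single-coefficient calculation to two other quantities and misidentifies the weakest tests.

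- **Categorical moderators.** The detectable slope difference is about twice the stated beta, and power at the stated beta is about 27–29%.
- **Product-term coefficients.** The tabled beta holds only on the standardized product-term scale, which the text does not specify.
- **Mediation.** The table gives no valid detectable indirect effect. Actual power runs from about 37% to near 100% across the path sizes and readings shown, excluding the very unequal paths noted above, so low power for Aim 2 in general is not established.

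The figures assume two-sided alpha 0.05, the effective sample sizes as tabled, and equal predictor and residual variance across groups. They make no allowance for unequal weighting, which the plan itself says may reduce power.

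**What to change.** 1. Remove the statement that rows 1 and 2 cover mediation and moderation, and change the table header to match.
2. Add rows for slope differences using the values in the table above, and state the scale on which interactions with continuous moderators are powered.
3. Correct the lowest-powered sentence: slope differences between groups are less powered than the simple slopes.
4. Add an indirect-effect row that states the assumed size of each path, uses the panel sample for Time 1 to Time 2 paths, and uses the number of families for the first path where exposure and mediator are both family-level.
5. Optionally, test indirect effects with percentile bootstrap intervals that resample whole families, in place of a z-test on a bootstrap standard error.

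The cost is restated text, extra table rows and less favourable stated figures. No new data are needed.

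### Table 1's .80 power is for a single coefficient but is extended to mediation products; with both paths at the tabulated beta, indirect-effect power is about 64% or 37–41%, depending on the test

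*Protocol article*

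**What the plan says.** The section on sample size determination defines the powered quantity: "Power is estimated for a standardized regression coefficient in a model with 5 covariates and alpha = 0.05". It adds: "Effect sizes detectable at .80 power are listed in Table 1". Effective sample sizes are derived "using an estimated within-family ICC = 0.30", giving "effective n = 1095 / 822 / 1917" for family-level predictors (row 1) and "effective n = 2034 / 1526 / 3560" for child-level predictors (row 2), in the order cross-sectional / panel / repeated measures. The detectable betas are 0.085 / 0.098 / 0.064 and 0.063 / 0.072 / 0.047.

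The header of Table 1 names mediation alongside direct and moderation effects. The text under the table says that the power of tests 1 and 2 covers direct effects, moderating effects and "mediation effects (products of path coefficients" for Aim 2.

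The analysis section for Aim 2 tests each indirect effect with an Mplus command "which employs a product of coefficients method of testing mediation", with bootstrap standard errors for the significance test. Mediators are taken at Time 1 and youth adjustment at Time 2. The article reports no separate power calculation for an indirect effect.

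**The concern.** A one-coefficient calculation is presented as the power of a two-coefficient test. An indirect effect is the product of the exposure-to-mediator path and the mediator-to-outcome path, and uncertainty in either one weakens the test. A beta that is detectable with .80 power on its own does not carry that power over to a product of two such betas.

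Mediation is one of three aims, with four pathways tested together to show which of them matter. A reader who accepts the stated .80 could give too much weight to a non-significant pathway whose two paths are near the tabulated size.

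**Working it through.** **1. Reproduce Table 1.** The inputs are F = 712 / 534 / 1246 families, two children per family, ICC 0.30, alpha 0.05 (only a two-sided test reproduces the table) and power .80.

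- Family level: effective n = 2F/(1 + 0.30). For F = 712, 1424/1.30 = 1095.
- Child level: effective n = 2F/(1 − 0.30). For F = 712, 1424/0.70 = 2034.
- Detectable beta = (1.960 + 0.842)/√(effective n) = 2.802/√(effective n). For 1095 this is 0.0847.

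All six effective sample sizes reproduce, and all six betas agree to within 0.001 (table below). A noncentral F check with 5 covariates gives power 0.80–0.81 at the printed betas. Rows 1 and 2 are therefore one-coefficient figures with no allowance for a second path.

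**2. Power of the indirect effect with both paths at the tabulated beta.** Each path estimate, in standard-error units, is drawn as an independent normal with mean 2.80 (4 million draws). Call the two values A and B.

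- Joint significance, |A| and |B| both above 1.96: 0.80 × 0.80 = 0.64.
- Product over first-order standard error, |AB|/√(A² + B²) > 1.96: 0.41.
- Product over a bootstrap-type standard error, |AB|/√(A² + B² + 1) > 1.96: 0.37.

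A full bootstrap simulation (n = 822, both paths 0.098, 1,500 replicates, 500 resamples) gave 37.5% for the z-test with bootstrap standard error and 64% for the percentile interval.

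**3. One path stronger.** Hold one path at its detectable size and set the other to twice its own. Power is then 0.80 (joint), 0.75 (first-order) and 0.74 (bootstrap-type). At three times it is 0.80 / 0.78 / 0.78. Power tends to .80 and does not exceed it.

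**4. The tabulated beta read as the product.** Two equal paths would each be √0.085 = 0.29 (cross-sectional, family level), or 0.22 to 0.31 across the six cells. Power is then near 100%, so .80 is not the power for that product either.

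**5. Equal paths needed for .80.** The required path size in standard-error units is 3.21 for the joint test (each path then has power √0.80 = 0.894) and 3.68 for the product over bootstrap-type standard error. Each is divided by √(effective n):

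| Cell | Effective n | Table 1 beta | 2.802/√n | Needed per path, product/bootstrap SE | Needed per path, joint or percentile |
|---|---|---|---|---|---|
| Family, cross-sectional | 1095 | 0.085 | 0.0847 | 0.111 | 0.097 |
| Family, panel | 822 | 0.098 | 0.0977 | 0.128 | 0.112 |
| Family, repeated | 1917 | 0.064 | 0.0640 | 0.084 | 0.073 |
| Child, cross-sectional | 2034 | 0.063 | 0.0621 | 0.082 | 0.071 |
| Child, panel | 1526 | 0.072 | 0.0717 | 0.094 | 0.082 |
| Child, repeated | 3560 | 0.047 | 0.0470 | 0.062 | 0.054 |

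**6. Power at 0.10 per path**, the size the article reports as a conventional small effect (joint / first-order / bootstrap-type):

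| Cell | Power |
|---|---|
| Family, cross-sectional | 0.83 / 0.67 / 0.64 |
| Family, panel | 0.67 / 0.44 / 0.40 |
| Family, repeated | 0.98 / 0.97 / 0.96 |
| Child, cross-sectional | 0.99 / 0.98 / 0.97 |
| Child, panel | 0.95 / 0.89 / 0.87 |
| Child, repeated | above 0.99 for all three |

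With 0.18 on both paths, power exceeds 0.99 in every cell for every test.

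**The case against.** The strongest reply is that the sentence is loosely scoped rather than wrong. If the tabulated beta is read as the smallest detectable weaker path when the other path is clearly stronger, the claim is nearly true (step 3). This stands as far as it goes. A reader might infer that no interpretation supports the statement, or that 64% is a ceiling on Aim 2 power; both inferences hold only for two equal, borderline paths. What remains is that the article never states the condition under which its claim would be approximately right.

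A second reply is that the study is planned around larger effects: the article cites betas of 0.18 to 0.32, at which power is ample. This limits the practical consequence. However, those betas are effects of deployment on youth outcomes, and the article gives no figure for deployment-to-mediator or mediator-to-outcome paths.

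Third, the repeated-measures sample is named as the priority sample, and its cells hold up at 0.10 per path. But the Aim 2 analysis takes mediators at Time 1 and outcomes at Time 2, which points to the panel column.

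Fourth, a journal article may leave a detailed mediation power calculation to a fuller document. That is accepted: the point is what the article states, not the missing calculation. The plan's emphasis on effect sizes and confidence intervals also makes it less likely that null pathways will simply be dismissed.

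**Conclusion.** The concern holds in limited form. The effective sample sizes and betas in rows 1 and 2 are arithmetically sound for one coefficient. The error is in attributing their .80 power to mediation products. With both paths at the tabulated beta, power is about 64% under a joint or percentile-interval test and 37–41% under the product-over-standard-error test described for Aim 2.

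At 0.10 per path the shortfall is confined to the family-level panel (40–67%) and family-level cross-sectional (64–83%) cells. The remaining cells are at about 87% or more. A reader might infer that Aim 2 as a whole is underpowered or that the sample is too small. The documents do not support this, because the true path sizes are not given and power is high at the larger effects cited.

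These figures assume independent path estimates, the article's own effective sample sizes, and the same row and column of Table 1 for both paths. The unequal weighting effect, which the article acknowledges, would lower power further; the article expects latent variables and control variables to raise it.

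**What to change.** Either remove mediation effects from the sentence under Table 1 and from the table header, or state there that rows 1 and 2 are single-path betas and that power for an indirect effect also depends on the second path.

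Then restate the detectable indirect effect at .80 power for the test named under Aim 2, giving both path sizes. For equal paths and a product test with bootstrap standard errors, the beta needed per path (cross-sectional / panel / repeated) is about 0.111 / 0.128 / 0.084 at family level and 0.082 / 0.094 / 0.062 at child level. If inference will instead use a joint test or percentile interval, the article should say so and give about 0.097 / 0.112 / 0.073 and 0.071 / 0.082 / 0.054.

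The cost is wording and a few table entries, and a less favourable stated power for Aim 2. Sample size, data collection and the planned analysis are unaffected.
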